### Outcomes

The primary endpoint for the first aim of the study (to investigate the therapeutic effects of the administration of N_2_O as a single-dose inhalational anaesthetic, phase A) is the assessment of mood symptoms approximately 24 h after administration. Mood symptoms will be measured using psychometric instruments, including the BDI, HDRS and CDRS-R. Further endpoints will be mood changes after 6 weeks (secondary endpoint) and 12 weeks (tertiary endpoint). For the second and third aims of the study (to determine whether the additive effects of N_2_O and SSRI administration provide a clinically significant improvement in mood over and above the benefits from SSRI administration alone [Phase B] and to investigate N_2_O as a possible predictor of SSRI treatment response, respectively), the endpoints will be measurements of mood (indicated by the BDI, HDRS and CDRS-R) at the weeks 6 and 12 follow-up.

### Recruitment

Participants will be recruited from PMH. Referrals to the study will also be accepted from general practitioners, local paediatricians and local developmental services, as well as from Headspace clinicians (Headspace is an early intervention service for youth with mental health disorders). Participants who discontinue the study will be not be replaced.

### Blinding procedure and assignment of condition

The personnel and the location for providing N_2_O-based treatment, as well as the psychiatric team and related locations for psychiatric examinations, will be completely separated. Medical records for N_2_O/placebo administration will be kept separate from the psychiatric assessment case report forms until completion of the entire trial. Participants and their families will be blinded to the nature of the inhaled gas and will be informed that they can receive either one or the other of the two conditions during phase A. Group assignment to either N_2_O or placebo will be performed by a clinical pharmacist using a random number generator for all participants. Randomisation according to this generator will occur on a 1:1 basis with a permuted block randomisation schedule created by the PMH Pharmacy Department. Apart from the inhalational mixture, the sessions for administration of N_2_O and placebo will be indistinguishable in regard to their setting, setup and monitoring.

The order of group assignment will be kept in a secure location. Each allocation will be sealed in individual envelopes and stored in order. Individual envelopes will be opened only upon the arrival of the participant for the administration of N_2_O or placebo mixture. The only person who has access to the random group allocation will be the study nurse and/or study anaesthetist who will administer the inhalational treatment or placebo in theatre. At the end of each treatment day, the group allocation protocol and treatment supply log will be resealed and kept in a secure location. This will be the only role for the nurse/anaesthetist, who will have no contact with the psychiatric team or the patient/family throughout the study duration to ensure continuous blinding. N_2_O and medical air will be supplied by piped theatre supply from PMH (regulated by biomedical services) and not via cylinders. The nature of the gas will therefore be obscured and known only to the study nurse/anaesthetist. The study will be unblinded only in the unlikely occurrence of an adverse event requiring unblinding to ensure patient safety.

### Data preparation and statistical analysis

This trial will yield data relating to the participants’ demographics, medical history, measures of mood during phase A and phase B, and blood samples indicating fluoxetine levels during phase B of the trial. All data will be de-identified upon collection, will be entered by one designated person on the research team, and will be securely stored. Only the research team will have access to the data. Hard copies of the data and questionnaires will be kept in a locked cabinet in a locked room within a secure building.

The primary outcome measure (HDRS) will be statistically analysed using a between-subjects mixed effects linear model. Dose-response curves will also be plotted for both groups (i.e., group that received N_2_O and the group that received the placebo gas). Any differences between the two dose-response curves may highlight the difference between the interventions received in phase A. Because this is a pilot study, each group will have a maximum of 15 participants. These analyses will also be repeated for the BDI and HDRS scales. Additionally, correlational analyses (Pearson’s/Spearman’s rho, depending on data distribution) between fluoxetine levels and relevant symptom changes (HDRS and BDI) will be calculated. SPSS software (IBM, Armonk, NY, USA) will be used for these analyses.

Power analysis using G*Power showed that a sample size of 30 participants detecting effect sizes of *f* = 0.25 with an α error = 0.05 will produce power of 0.75 when using analysis of variance with repeated measures (within-between factors, number of measurements = 1, correlation among repeated measures = 0.5, non-centrality parameter λ = 7.5, critical *F* = 4.20, numerator *df* = 1, denominator *df* = 28). Whilst the power of the present study is slightly less than the conventional 0.08, it is noted that this is a pilot study, and it is anticipated that these data will inform future investigations with larger sample sizes.

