### Subjects and eligibility criteria

In this study, we aim to recruit a total of 30 participants. There are three key inclusion criteria. First, participants must have a confirmed diagnosis of moderate to severe major depressive disorder according to the International Classification of Diseases, Tenth Revision, or the *Diagnostic and Statistical Manual of Mental Disorders, Fifth Edition*, criteria, with the diagnosis to be confirmed through the administration of the Kiddie Schedule for Affective Disorders and Schizophrenia (K-SADS) [18] as well as a full psychiatric assessment. Second, participants must be aged between 12 and 17 years. Third, participants and their parents/guardians must agree to start fluoxetine as treatment in phase B of the study. Exclusion criteria include any active suicidal ideation or plans, current use of other psychiatric medications at study entry, IQ < 85 (screened using the Wechsler Abbreviated Scale of Intelligence [WASI-II] [19]), active or past diagnosis of an eating disorder, current or recent (i.e., past 12 months) abuse or dependence on alcohol or illicit substances, current pregnancy in female participants, significant chronic medical or neurological disorder, history of bipolar disorder, schizophrenia, schizoaffective disorder, obsessive compulsive disorder or personality disorders, presence of an acute medical illness that could interfere with study participation, active psychotic symptoms, administration of NMDA receptor antagonists during the preceding 3 months, ongoing or past treatment with electroconvulsive therapy, contraindications against the use of N_2_O and contraindications against the use of fluoxetine.

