#### Psychological assessments that will be conducted in phase A

As outlined in Fig. 1, a number of psychological assessments will be conducted in phase A, immediately pre-intervention and 2 h and 24 h after N_2_O or placebo administration. These include the BDI, HDRS, and CDRS-R. The CBCL, YSR and Clinical Global Impression (CGI) will be completed immediately pre-intervention.

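### The named primary HDRS model and the test behind the 0.75 power do not match; a 24 h contrast adjusted for pre-intervention HDRS would settle this and raise power to about 0.86 on the protocol's inputs

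*Protocol article*

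**What the plan says.** All from the protocol article.

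- *Data preparation and statistical analysis*, on the model: "The primary outcome measure (HDRS) will be statistically analysed using a between-subjects mixed effects linear model". The section names no covariate and no tested term.
- Same section, on power at N = 30: "detecting effect sizes of *f* = 0.25 with an α error = 0.05 will produce power of 0.75". The test assumed for this figure is given there as follows: "when using analysis of variance with repeated measures (within-between factors". The other entries are number of measurements 1, correlation 0.5, λ = 7.5, critical F = 4.20, and 1 and 28 degrees of freedom. The authors acknowledge that the power is below convention and point to the trial's pilot status.
- *Outcomes*: the primary endpoint for the first aim "is the assessment of mood symptoms approximately 24 h after administration".
- *Psychological assessments that will be conducted in phase A*: the HDRS is rated "immediately pre-intervention and 2 h and 24 h after N_2_O or placebo administration".
- Size and allocation: "In this study, we aim to recruit a total of 30 participants" (*Subjects and eligibility criteria*); "each group will have a maximum of 15 participants" (*Data preparation and statistical analysis*); "Randomisation according to this generator will occur on a 1:1 basis" (*Blinding procedure and assignment of condition*).

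**The concern.** One section describes the primary analysis in two ways. The model sentence speaks of a between-subjects analysis. The power sentence rests on whether the arms change differently over time. With three phase A ratings these can be different tests with different power, and a reader cannot tell which one the 0.75 belongs to. The printed number of measurements adds to the doubt, since one measurement leaves no time factor to interact with.

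Two things are at stake. First, the visit-averaged arm effect, the arm-by-time interaction, the change score and the adjusted 24 h contrast all fit under the heading of a mixed model; naming one in advance removes the choice after the data are seen. Second, the trial already collects a pre-intervention HDRS, and the protocol's own correlation implies that using it as a covariate is worth a material gain in a study of 30 that concedes it is short of power.

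**Working it through.** **Inputs from the article.** N = 30, 15 per arm, 1:1; f = 0.25; α = 0.05; ρ = 0.5; printed λ = 7.5; df 1 and 28; stated power 0.75. k = 2 arms; m = number of measurements.

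**Step 1. Reproduce the stated power.** For the within-between interaction, λ = f²·N·m/(1 − ρ), with df (k − 1)(m − 1) and (N − k)(m − 1).

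- m = 1, as printed: λ = 0.0625 × 30 × 1/0.5 = 3.75, with 0 numerator df. This is not the printed result.
- m = 2: λ = 0.0625 × 30 × 2/0.5 = 7.5, df 1 and 28, critical F 4.196, power 0.753. This matches every printed output.

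A between-subjects F test with the same f has λ = f²·N·m/(1 + (m − 1)ρ), which is 1.875 at m = 1 and 2.5 at m = 2. Neither is 7.5. So the 0.75 belongs to the group-by-time test with two measurements, that is, one before and one after the gas.

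**Step 2. The effect this implies.** In a 2 × 2 layout, f = 0.25 means interaction effects of ±0.25 SD in the four cells, so the difference between arms in change is 4 × 0.25 = 1.0 SD. The article does not state this value; it is derived, and it requires m = 2. Check: the change has variance 2(1 − ρ) = 1.0 in SD² units, so λ = (15/2) × 1.0²/1.0 = 7.5.

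**Step 3. Three ways of testing the same 1.0 SD difference.**

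- Change score: λ = 7.5/[2(1 − ρ)], df 1 and 28.
- 24 h score alone: λ = 7.5, df 1 and 28; power 0.753 at any ρ.
- 24 h score adjusted for pre-intervention HDRS: λ = 7.5/(1 − ρ²), df 1 and 27.

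| ρ | Change: λ | Change: power | Adjusted: λ | Adjusted: power |
|---|---|---|---|---|
| 0.3 | 5.36 | 0.61 | 8.24 | 0.79 |
| 0.5 (protocol) | 7.50 | 0.75 | 10.00 | 0.86 |
| 0.7 | 12.50 | 0.93 | 14.71 | 0.96 |

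**Step 4. Chance imbalance.** The adjusted formula takes the arms as balanced at baseline. A simulation of 200,000 trials at ρ = 0.5, with baseline left to chance, gives 0.849 for the adjusted test and 0.753 for the change score.

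**Step 5. Loss.** The article gives no dropout rate. As an assumption, 20% loss leaves N = 24. At ρ = 0.5 the change score then has λ = 7.5 × 24/30 = 6.0, df 1 and 22, power 0.65. The adjusted test has λ = 10 × 24/30 = 8.0, df 1 and 21, power 0.77.

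**The case against.** The article condenses a longer protocol. Covariates, fixed effects and the exact contrast are often left to that document or to an analysis plan, so their absence here does not show that the trial does without them. The 24 h target is not missing either, because the Outcomes section fixes it. And "between-subjects" may mean only that arm is a parallel-group factor; a mixed model can still hold visits, an arm-by-visit term and the baseline.

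All of that stands. It limits the point, but it does not remove the mismatch between the model label and the powered test, or the impossible number of measurements, since those statements are printed in the article itself.

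A reader might go further and infer that the primary test is an arm effect averaged over all visits, including the rating before any gas is given, and so is severely underpowered. The article does not support this. It nowhere says that the tested term is a visit average or that the pre-intervention score enters as a response. Any power figure for that reading would also need an assumed effect at 2 h, which the article does not give. Nor is a visit-averaged test necessarily weak. Averaged over 2 h and 24 h only, with an equal 1.0 SD effect at both, the variance is (1 + 0.5)/2 = 0.75, so λ = 7.5/0.75 = 10 and power is again about 0.86.

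**Conclusion.** The point holds in a limited form. The primary model as labelled and the test behind the stated power should be reconciled, and the printed number of measurements should be 2 if the other outputs are right. Adjusting a named 24 h contrast for the pre-intervention HDRS is then a worthwhile improvement: about 0.86 (0.85 with chance imbalance) against 0.75 for the change-score test on the protocol's inputs.

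The comparison is with the change-score test, or equally the 24 h score alone at ρ = 0.5. It is not with a fully defined primary model, because the article does not define one. The gain rests on ρ = 0.5 and on the derived 1.0 SD difference. Adjustment does better than the change score at each correlation shown, but clearing 0.80 is conditional: at ρ = 0.3, or with an assumed 20% loss, the adjusted test falls slightly short. This is a recommended correction and not evidence that the trial cannot answer its question.

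**What to change.** Replace the model sentence with, for example: *The primary analysis is the difference between arms in HDRS at 24 h, with 95% confidence interval, from a linear mixed model of the 2 h and 24 h scores with arm, visit, arm-by-visit and pre-intervention HDRS as a covariate.*

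Then restate the power for that contrast, giving the assumed difference in SD units, the correlation between pre-intervention and 24 h HDRS, and any allowance for loss. If the repeated-measures calculation is kept for reference, correct the number of measurements to 2 and say that it refers to the change-score (group-by-time) test. If the full protocol or analysis plan already specifies a baseline-adjusted 24 h contrast, only the label and the power statement need to be aligned with it.

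The cost is two rewritten sentences and one degree of freedom. No participants, visits or ratings are added.

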### Trial management

This trial will be managed by [name] and [name], with assistance from [name] and [name]. Stringent records will be kept in a master file and will include records of adverse events. In the unlikely event of an adverse event, records will be submitted by a study-specific data and safety monitoring committee, and committee members will be independent of the study team. With regard to the possible occurrence of an adverse event in phase A, N_2_O is widely used and has minimal side effects that are usually transient and vary between individuals. However, participants who experience an adverse event following the N_2_O or placebo administration will be followed in the recovery area and assessed and managed by a consultant anaesthetist until they are stable and cleared for discharge from the hospital. The chief investigator will be informed of the adverse event as soon as possible after its occurrence. All participants will be continuously monitored, and treatment with N_2_O and placebo will be conducted in a theatre with a high degree of supervision. A medical practitioner will be available at all times to assess and manage side effects if they emerge. For example, an ondansetron sublingual wafer (4–8 mg depending on weight) will be available to treat nausea and vomiting during the study period.

Stopping rules have also been developed for this trial, and the development of these rules has been done taking into consideration common and serious adverse events which can occur in adolescents being treated for a major depressive episode with antidepressant medication. Because it may be difficult to disentangle whether an adverse event is due to treatment or part of the depressive disorder, this study will be halted and reviewed if the following number of adverse events occur: an event of a completed suicide, two events of attempted suicide, four individual reports of an increase in non-suicidal deliberate self-harm, three individuals reporting the development of hypomania or two patients reporting the development of mania, and one report of severe psychotic symptoms requiring hospitalisation or intensive community-based treatment. The rates of the following possible adverse events have been estimated from the Treatment of Adolescent Depression Study [21], because it has published results based on the largest available cohort of comparable patients. If patient symptoms worsen during the trial, they may be excluded from the study and will not be replaced. However, they will receive a care plan, and the study doctors will facilitate access to community-based mental health care.

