#### Biochemical and psychological assessments that will be conducted in phase B

Blood samples will be taken during weeks 4, 8 and 12 of phase B. These blood samples will be used to assess compliance with the fluoxetine treatment. These samples will contribute to the investigation of the relationship between mood changes and the data relating to N_2_O/placebo administration. Compliance with fluoxetine treatment will also be monitored through empty packet return and patient report. Blood samples will undergo basic laboratory processing before storage in a lockable −80 °C freezer.

Psychological assessments will be conducted on a weekly basis and will include the BDI, HDRS and CDRS. The CBCL, YSR and CGI will be completed during the weeks 6 and 12 follow-up. Measures obtained from the CBCL and the YSR during the weeks 6 and 12 follow-up will be used for additional clinical monitoring purposes. Participants are also permitted to continue their normal mental health TAU, which may include engagement in cognitive behavioural therapy or other forms of psychotherapy for depression. As per recommendation by the local ethics committee, the study does not either prescribe or restrict participation in psychological therapy. This is at the discretion of the participants and their treating clinicians. The type of psychological therapy and number of sessions over the study period will be recorded for each participant on the basis of a report from the participant’s treating clinician. Access to other treatment strategies will be accounted for in the statistical analysis of the data and will be reported upon completion of the study.

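### Excluding participants because their symptoms worsen makes week 6 and 12 mood data missing on account of the outcome, with no provision for further ratings

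*Protocol article*

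**What the plan says.** Trial management, after the rules for halting the study: "If patient symptoms worsen during the trial, they may be excluded from the study and will not be replaced". The next sentence says what such participants are offered: "However, they will receive a care plan, and the study doctors will facilitate access to community-based mental health care". It does not mention further outcome assessment. The article gives no threshold, instrument, time window or decision-maker for worsening.

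Outcomes: for the second and third aims, "the endpoints will be measurements of mood (indicated by the BDI, HDRS and CDRS-R) at the weeks 6 and 12 follow-up". The same two time points are also the secondary and tertiary endpoints of the first aim, whose primary endpoint is mood about 24 h after the gas.

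Phase B assessments: "Psychological assessments will be conducted on a weekly basis and will include the BDI, HDRS and CDRS". Recruitment: "Participants who discontinue the study will be not be replaced". Data preparation and statistical analysis: the HDRS "will be statistically analysed using a between-subjects mixed effects linear model", with at most 15 participants per group.

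**The concern.** The trigger for leaving the study is the quantity that the study measures. The scales used for the endpoints are rated every week, so deterioration is visible before week 6 or week 12 is reached, and the participants who show it may then stop contributing data. If nitrous oxide has a lasting benefit, more of them will come from the placebo arm, and those still followed in the two arms are no longer comparable. Blinded, even-handed use of the rule does not prevent this.

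Three results are exposed: the arm difference at weeks 6 and 12, the mean improvement within each arm, and the analysis of whether the early response predicts SSRI response, which needs the poor responders in its range. The randomised treatment is a single one-hour inhalation that is over before phase B begins, so ending follow-up in phase B cannot withdraw it. The care decision and the collection of ratings can be separated.

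**Working it through.** **Plan's own figures.** The article gives no exclusion rate and no figure for this bias. Its only related number is the power. With λ = 7.5, df 1 and 28 and critical F = 4.20, the non-central F gives 0.753, matching the stated 0.75. No allowance for loss is stated. As a rough indication, scaling λ as 7.5 × N/30 gives power of 0.72 at N = 28 and 0.69 at N = 26.

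**Step 1. Only remaining participants analysed, exclusion on the endpoint change.** These inputs are assumptions. Improvement is normal in units of its own SD, with mean μ = 1.0 for placebo and 1.5 for nitrous oxide (true difference 0.50). Everyone below a cut c is excluded and all their data are dropped.

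- Fraction excluded: Φ(c − μ)
- Mean of those remaining: μ + φ(μ − c)/Φ(μ − c)

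| Cut c | Excluded, placebo / N2O | Mean remaining, placebo | Mean remaining, N2O | Observed difference |
|---|---|---|---|---|
| 0 | 15.9% / 6.7% | 1.0 + 0.2420/0.8413 = 1.288 | 1.5 + 0.1295/0.9332 = 1.639 | 0.351 (−30%) |
| −0.5 | 6.7% / 2.3% | 1.0 + 0.1295/0.9332 = 1.139 | 1.5 + 0.0540/0.9772 = 1.555 | 0.416 (−17%) |
| −1.0 | 2.3% / 0.6% | 1.0 + 0.0540/0.9772 = 1.055 | 1.5 + 0.0175/0.9938 = 1.518 | 0.462 (−8%) |

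With 15 per arm, the first row is about 2.4 against 1.0 persons. The last is 0.3 against 0.1.

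At the cut of 0, other assumed means change the shrinkage:

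- 0.5 versus 1.0 SD gives 1.288 − 1.009 ≈ 0.278 (−44%).
- 1.5 versus 2.5 SD gives 2.518 − 1.639 = 0.879 (−12%).

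**Step 2. Exclusion on an earlier weekly score.** Simulation with 2,000,000 per arm and correlation 0.5 between visits, so that change has SD 1. Placebo improves by 0.5 SD at the earlier visit and 1.0 SD at week 6. Nitrous oxide is 0.5 SD better at both. Participants above their own baseline at the earlier visit are excluded.

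| Share of worsened excluded | Excluded, placebo / N2O | Difference, remaining only | Difference, earlier scores kept in a likelihood model |
|---|---|---|---|
| All | 31% / 16% | 0.39 | 0.50 |
| Half | 15% / 8% | 0.46 | 0.50 |

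The last column is free of bias because exclusion there depends only on scores that were recorded and kept.

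**Step 3. No true difference, same rule in both arms.** The arm difference stays at 0. A within-arm improvement of 1.00 SD appears as 1.25 (all worsened excluded) or 1.10 (half).

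**The case against.** A reader might infer that the week 6 and 12 results will certainly be computed on a sample stripped of its worst outcomes. The article does not say that. It does not state that collected scores are deleted or that only completers are analysed, and it names a mixed effects model alongside weekly ratings. Step 2 shows that such a model can recover the difference. This much stands, but it needs two conditions that the article does not give: that earlier scores are kept, and that exclusion depends only on recorded scores. A discretionary clinical judgement does not guarantee the second. Handling of withdrawn participants' data may well be set out in the full protocol or an analysis plan, and its absence from an article is no fault. But an analysis cannot use ratings that were never taken, and the exclusion sentence itself is stated here.

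The 30% shrinkage is also close to a worst case. The rule is optional, and its place beside halting rules for suicide attempts, mania and psychosis suggests serious deterioration rather than any change below zero. Even the largest loss in the main example, 0.15 SD, is about 0.4 of the standard error of the difference at 15 per arm (√(2/15) = 0.365 SD).

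Two further inferences are not supported. One is that the rule could manufacture a benefit: every example with a true effect shrinks it, even use under no effect leaves the contrast at zero, and the psychiatric team is kept apart from the allocation. The other is that harm would be hidden: adverse events are recorded separately and go to an independent committee, and serious psychiatric events count toward halting. Only deterioration on the rating scales after exclusion could be missed.

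**Conclusion.** The point holds for weeks 6 and 12. As written, the rule allows outcome data to be lost because of the outcome, and nothing else in the article limits it. If nitrous oxide works and only those remaining are analysed, the bias runs toward no difference. Within-arm improvement is overstated whether or not there is an effect, and the predictor analysis loses part of its range.

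The article cannot supply the size. Under the stated assumptions a true 0.50 SD is seen as 0.35 to 0.46, depending on how severe the worsening must be, and as about 0.50 under the favourable conditions of the mixed model.

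The 24 h primary endpoint is measured before fluoxetine starts and is largely untouched. Aims 2 and 3 are framed as exploratory within a pilot. This is therefore a should-fix. It still matters because the article expects these data to inform larger studies, and missing ratings cannot be recovered afterwards.

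**What to change.** Leave the clinical decision and the care plan exactly as they are. Replace exclusion from the study with continued follow-up, for example:

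> With consent, participants whose symptoms worsen continue the scheduled HDRS, BDI and CDRS-R ratings, at least at weeks 6 and 12. All scores already collected are kept, and all randomised participants are analysed in their assigned group. The number of participants who stop follow-up, and the reasons, are reported by arm.

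If the full protocol already provides for this, the article's sentence should be brought into line with it. The cost is a wording change and a few extra ratings on the existing schedule.
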